### Power and sample size estimation

Cognitive training for patients undergoing heart surgery administered by de Tournay-Jette et al. (2012) [19] revealed medium-to-large effect sizes (*η*^2^ = 0.10–0.23). We have decided to use the smaller effect size (*η*^2^ = 0.10) for calculation so as not to underestimate the required sample size. Using this effect size, 37 patients per group are needed to obtain statistical power of 80% at a significance level of *p* = 0.05 (two-tailed). Based on previous cardiosurgical studies, we estimate a dropout rate of 20% between each of the four assessment time points. Thus, the number of study patients recruited at baseline assessment was fixed at 72 patients per group. For sample size and statistical power calculations, we used G*Power-3 analysis software.

### Data management

All personal information about enrolled patients will be subject to medical confidentiality. Paper-based assessment forms will be used to record the outcome variables. The data will be manually entered in an electronic database, which is password-protected and will be checked for quality and accuracy. All assessment forms, signed informed consent forms, and the randomization list will be stored in a locked cabinet.

### Dissemination policy

Our goal is to make the study results available to the general public, healthcare providers, and scientists by publishing them in the public press, at scientific congresses, and as original articles in peer-reviewed journals. The results will be reported regardless of the amount and direction of the effect.

## Discussion

The aim of this study is to evaluate a paper-and-pencil-based cognitive training program for patients undergoing heart surgery with extracorporeal circulation. POCD shows the highest incidence of neurological complications that can occur in the context of surgery, especially cardiac surgery [1]. Adverse effects of POCD on daily living abilities can be noticed by patients themselves and their relatives in both the short and long term [6]. The etiology remains controversial but can be considered a multifactorial event in which extracorporeal circulation plays a crucial role [8].

Here, we present cognitive training that integrates well with standard rehabilitation, takes place as early as possible, and aims to reduce the occurrence and persistence of cognitive deficits in the short and long term. It is also of interest whether patients with perioperative ischemic stroke benefit from this intervention to varying degrees or in different forms.

We intentionally opted for technically simple paper-and-pencil-based training tasks because POCD after cardiosurgical procedures mainly affects elderly people. Many studies on the effect of cognitive training have used computer-based training tasks [15], which provide the advantage of generating and capturing data simply, quickly and very precisely. However, even today, they often represent an unfamiliar medium for older people, which could lead to irritation, fear of contact, and/or frustration in the older population studied here and thus constitute a potential bias. A placebo intervention for the control group is intentionally omitted because cognitive effects of placebo interventions on cognitive performance are difficult to control. In order to credibly suggest to patients that the placebo intervention could have an influence on their memory and thus also to achieve a willingness to participate, the structure of the placebo intervention will have to be closely related to cognitive training (e.g., relaxation exercises, crossword puzzles, conversation therapy, computer games, etc.) and thus also achieve cognitive training effects.

The only prospective investigation of patients undergoing cardiac surgery to date reported a beneficial effect of memory and attentional training in patients who underwent CABG [19], but no information was given on the use of extracorporeal circulation in this collective. In this study, training took place between the 6th and the 10th week following surgery. However, it is still not clear when the optimal time point for cognitive training should be set and for how long the intervention should be carried out. It seems possible that the rehabilitation of postoperatively impaired cognitive function will be more improved by an earlier intervention starting in the range of a week compared to one month after surgery. Controlled studies on neurorehabilitation of post-stroke cognitive impairment have shown beneficial effects for several cognitive functions when restitutive cognitive training begins within 2 weeks [40] or about 7 months [17] after stroke onset. Animal models suggest a time-dependent increase in neuroplasticity (plastic window) after ischemic injury, with a peak at 7–14 days and near completion at 30 days. Nevertheless, it should be noted that the assignability of these findings from bench to bedside is difficult, and the shape and extent of the neuroplastic window in humans remains unclear [41].

In our study, the detection of acute, perioperative cerebral ischemia is performed by MRI with DWI. With the use of DWI, a preoperative baseline assessment is not necessary because in this sequence, acute ischemic tissue is presented as a bright area that typically occurs 2–3 h after the onset of damage and usually subsides within 2–3 weeks [42]. These acute cerebral ischemic lesions can be detected by DW-MRI in 14–61% of the patients after cardiac surgery [11, 43]. The significance of those acute MRI lesions, especially with regard to manifestation of POCD, remains unclear [42]. To our knowledge, there are no studies controlling for the potentially confounding effect of peri-interventionally endured cerebral ischemia detected during the first postoperative week. In this context, it seems of particular interest whether patients with acute cerebral ischemia benefit from cognitive training to any other degree or in any other form.

So far, increased efforts have been made to prevent POCD, addressing anesthesia, cardiotechnology, and cardiac surgery [9], with limited but measurable success; these procedural preventive measures alone can reduce the incidence of POCD in the magnitude of 30% [44]. In contrast to procedural prevention strategies, the concept of cognitive training allows the patient to act independently, responsibly and actively. This can perhaps exert a positive effect on the recovery process through the experienced self-efficacy that seems to contribute to better recovery after heart surgery in terms of patients’ worries, energetic mood, reading, ambulating, and fitness [45]. With the knowledge that cognitive deficits can be actively addressed afterward, the fear of surgery can possibly be reduced; finally, one must not forget the drastic experience of a potentially life-threatening cardiac disease. Preoperative anxiety has been shown to be a predictor of major morbidity and mortality in patients who have undergone heart surgery [46].

The present investigation certainly contains some limitations. First of all, participation in the study is tied to the performance of a heart operation using a heart-lung machine. A comparison with patients undergoing off-pump cardiac surgery is therefore not possible. Given the lack of knowledge about the optimal starting time or duration of training, the intervention may be too early or the duration of approximately 3 weeks too short. It could also be discussed as to whether an additional follow-up investigation after several years would provide further valuable information on the long-term course of POCD and the training effects. For the aforementioned reasons, no placebo intervention is planned in the present study; this may formally affect the quality of the study and the transferability of the results. Finally, our cognitive training consists of a combination of validated [36] and unvalidated tasks. Since our self-created tasks are not validated, we do not know whether they might potentially contribute to an alteration in cognition.

The results of our study could have potentially important implications for the prevention and treatment of POCD. In particular, if our cognitive training is feasible and effective in maintaining or improving cognition and quality of life, it could be integrated into the treatment programs of rehabilitation centers that treat patients after heart surgery. Economically and organizationally, this is possible without much effort because the cognitive exercises are independently workable and need no great control, and rehabilitative centers usually have psychologists who could be involved in the organization of the exercises, distribution of tasks, or clarification of questions. Furthermore, the cognitive training is designed in such a way that it could also be carried out in an ambulant setting.

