### Magnetic resonance imaging

Cranial MRI will be performed 6–10 days after surgery using a 3-T scanner (Skyra; Siemens, Erlangen, Germany). The protocol of imaging will include a T2-weighted turbo spin-echo sequence (slice thickness = 3 mm, field of view (FOV) = 220 × 220 mm, matrix = 512 × 391, repetition time (TR) = 7490 ms, echo time (TE) = 100 ms), a T2-weighted turbo spin-echo sequence for dark fluid (slice thickness = 3 mm, FOV = 220 × 220 mm, matrix = 320 × 224, TR = 7000 ms, TE = 81 ms), a T1-weighted FLASH sequence (slice thickness = 3 mm, FOV = 220 × 220 mm, matrix = 320 × 320, TR = 250 ms, TE = 2.49 ms) and a diffusion-weighted echo-planar imaging sequence (slice thickness = 3 mm, FOV = 220 × 220 mm, matrix = 160 × 160, TR = 7720 ms, TE = 64 ms, slice gradients of *b* values = 0 and 1000 s/mm^2^). The postoperative diffusion-weighted sequence will be used by two blinded, experienced observers for registration and planimetric evaluation of acute ischemic lesions.

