### Secondary outcome measure

As a secondary outcome, we will evaluate the training effect of all objectively measured neuropsychological functions at 3 and 12 months after discharge from rehabilitation. Second, we will evaluate the training effect on the subjective self-assessment and external assessment by relatives of cognitive failures at 3 and 12 months after discharge from rehabilitation. Third, we will evaluate the training effect on HRQ at 3 and 12 months after discharge from rehabilitation. Fourth, we want to investigate the extent to which the cognitive training has an impact on depression at all follow-up time points. Last, we will examine the impact of perioperative cerebral ischemia on the neuropsychological measured training effect at all follow-up time points. Perioperative cerebral ischemia will be measured with postoperative DW-MRI during the first postoperative week. The number and size of ischemic lesions are determined and will be used as a control variable for the analysis of the training effect.

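### A single DWI scan on day 6–10 cannot secure the perioperative label: by the protocol's own visibility figures, a lesion may predate surgery by up to 4 to 15 days.

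*Protocol article*

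**What the plan says.** The protocol article plans one brain MRI per patient, after surgery. The Magnetic resonance imaging section says "Cranial MRI will be performed 6–10 days after surgery using a 3-T scanner", and Study design and enrollment and the Fig. 1 legend give the same window. The preoperative assessment, on the day before surgery, consists of cognitive tests and questionnaires without imaging.

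The Discussion justifies having no preoperative scan: "With the use of DWI, a preoperative baseline assessment is not necessary". The reason given is that acute damage shows up bright on this sequence, a signal that "typically occurs 2–3 h after the onset of damage and usually subsides within 2–3 weeks".

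On reading the scans: "The postoperative diffusion-weighted sequence will be used by two blinded, experienced observers for registration and planimetric evaluation of acute ischemic lesions".

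The Secondary outcome measure section names the exposure: "Perioperative cerebral ischemia will be measured with postoperative DW-MRI during the first postoperative week". The last paragraph of the Background describes the timing in the same way. Lesion count and size then serve the last secondary objective, the impact of ischemia on the training effect. In Planned statistical analyses they are also listed among the covariates of the additional repeated measures ANCOVA.

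**The concern.** A time-limited signal can date a lesion to the operation or later only if the signal lasts no longer than the time elapsed since the operation. Here it lasts longer. The stated reason separates acute from old tissue damage. It does not separate a lesion caused around surgery from one that arose shortly before it.

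At stake is what the last secondary objective can conclude. If some counted lesions predate surgery, the variable mixes preoperative and surgical ischemia, and a finding about surgery-related ischemia would not be secured. Some of these lesions may also predate the cognitive baseline, so part of their effect may already be in the baseline score. The Discussion presents control for peri-interventional ischemia as something no earlier study has done, so the label should match what the scan can show.

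The timing wording is a second, smaller problem. The Background and the Secondary outcome measure section place the scan in the first postoperative week. The three other places allow up to day 10.

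**Working it through.** **Inputs**

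- Visibility of a DWI lesion after onset: 2–3 weeks, that is 14–21 days (Discussion; qualified by *usually*).
- Scan day: 6 to 10 after surgery (Magnetic resonance imaging; Study design and enrollment; Fig. 1 legend).
- Cognitive baseline: 1 day before surgery (Study design and enrollment; Fig. 1 legend).

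The protocol states no look-back figure of its own, so there is none to reproduce.

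**Step 1. Look-back before surgery**

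Earliest onset still visible, in days before surgery = visibility − scan day.

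| Visibility | Scan day 6 | Scan day 7 | Scan day 10 |
|---|---|---|---|
| 14 days | 14 − 6 = 8 | 14 − 7 = 7 | 14 − 10 = 4 |
| 21 days | 21 − 6 = 15 | 21 − 7 = 14 | 21 − 10 = 11 |

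The range is 4 to 15 days. Every entry is positive, so the stated reason fails to exclude preoperative onset at every combination, including the most favourable one. Because the Discussion says *usually*, 21 days is not a hard ceiling.

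**Step 2. Look-back before the cognitive baseline**

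Subtracting the one day between baseline and surgery gives 4 − 1 = 3 to 15 − 1 = 14 days before the baseline test.

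**Step 3. Does another part of the protocol close the gap?**

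- Inclusion and exclusion criteria: stroke history and preexisting neurological disorders are excluded. That covers known disease, not a recent silent lesion.
- Magnetic resonance imaging: two blinded readers register acute lesions. A lesion from a few days before surgery can still look acute on this scan.
- Preoperative assessment: no imaging.
- Limitations paragraph of the Discussion: the point is not mentioned.

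**Step 4. Can the affected share be computed?**

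No. The only lesion frequency in the document is the 14–61% quoted in the Discussion for DWI lesions after cardiac surgery. It does not separate lesions by time of onset.

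**Step 5. Effect on the randomized comparison**

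The Randomization section places allocation after enrollment and the baseline assessment; the Fig. 1 legend places it after transfer to rehabilitation. On either reading, a lesion older than the baseline is also older than allocation. With blinded readers, mislabelled lesions should be balanced between the arms in expectation.

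**Step 6. Timing wording**

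The first postoperative week ends on day 7. Of the five scan days 6, 7, 8, 9 and 10, three (8, 9 and 10) fall outside it. Limiting the window to days 6–7 would give a look-back of 14 − 7 = 7 to 21 − 6 = 15 days, so this mismatch is separate from the attribution problem.

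**The case against.** The best defence is that the Discussion sentence is modest. A preoperative scan would mainly serve to separate fresh lesions from old infarcts, and DWI does that. What remains is a silent infarct within a short span before elective surgery, in patients without known stroke or neurological disease. Nothing in the document shows that this is common. The article may also leave lesion-reading criteria to the full protocol, and the T2, dark-fluid and T1 sequences are acquired alongside DWI.

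Much of this stands. The frequency is unknown and may be low, and the absence of a dating rule from an article is not held against the plan. The defence does not rescue the sentence itself, which offers the visibility window as sufficient reason and is contradicted by the scan schedule.

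Several stronger inferences are tempting but unsupported:

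- *A given percentage of lesion-positive patients is misclassified, and the lesion contrast shrinks by that percentage.* The document supplies no such share. Equal shrinkage would further assume that preoperative lesions have no effect at all.
- *Lesions from before surgery are irrelevant to the objective.* The objective concerns the response to training, which starts about a week after surgery. A lesion a few days older than surgery is still recent then and may modify that response.
- *The rate of surgery-related ischemia is overstated.* No such rate is an outcome of the trial.
- *The primary result is biased.* Step 5 of the working shows why it is not.
- *The Discussion repeats the timing error.* Its reference to the first postoperative week describes the literature, not this trial's scan.

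**Conclusion.** The point holds in limited form. On the protocol's own figures, a lesion counted as perioperative may have arisen up to 4 to 15 days before surgery, depending on visibility and scan day. The claim that DWI removes the need for a baseline therefore does not secure the label. Fifteen days is the extreme corner of that range, not a typical value.

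The consequence is confined to the interpretation of the last secondary objective and of the lesion covariates in the additional ANCOVA. Its size cannot be quantified from the document. The unadjusted comparison between arms, and with it the primary outcome, is not biased. The conclusion assumes only the stated 2–3 weeks of visibility and the stated scan window.

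The scan-timing descriptions contradict each other whatever is decided on attribution. The change is worth making because it is cheap and determines what the ischemia analysis can claim.

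**What to change.** No additional scan is required.

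1. Remove the statement that DWI makes a preoperative baseline unnecessary. Define the exposure as recent ischemia visible on DWI at the day 6–10 scan, and say that onset before surgery cannot be excluded. Limit conclusions about surgery-related ischemia accordingly.
2. Record from the chart any invasive cardiac or vascular procedure, or suspected embolic event, in the 15 days before surgery (the upper end of the computed range). Repeat the lesion analyses without those patients as a sensitivity analysis. State that this cannot detect all silent lesions, so an unchanged result would be reassuring but not conclusive.
3. Reconcile the first-week wording in the Background and the Secondary outcome measure section with the 6–10 day window in Study design and enrollment, the Fig. 1 legend and Magnetic resonance imaging. Leave the Discussion's sentence about the literature as it is.

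The cost is one chart item alongside the preexisting conditions already documented, one sensitivity analysis and some rewording. The only downside is slightly fewer patients in that sensitivity analysis.

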### Trial status

The study is currently enrolling patients. Recruitment started on 13 July 2016. Recruitment is expected to be completed in February 2020. Protocol version: 1.4 (10-08-2019).

## Data Availability

The datasets analyzed during the current study are available from the corresponding author on reasonable request.

## Abbreviations

AKT: Alterskonzentrationstest
ANCOVA: Analysis of covariance
ANOVA: Analysis of variance
CABG: Coronary artery bypass grafting
DW-MRI: Diffusion-weighted magnetic resonance imaging
FA: Fractional anisotropy
f-CFQ: Cognitive Failure Questionnaire for foreign assessment
FDR: False discovery rate
FOV: Field of view
HADS: Hospital Anxiety and Depression Scale
HQL: Health-related quality of life
ICU: Intensive care unit
MCI: Mild cognitive impairment
MRI: Magnetic resonance imaging
NVLT: Non-Verbal Learning Test
POCD: Postoperative cognitive decline
POCI: Postoperative cognitive improvement
RWT: Regensburger Wortflüssigkeits-Test
s-CFQ: Cognitive Failure Questionnaire for self-assessment
SKT: Syndrom-Kurztest
SVT: Symbolverarbeitungstest
TE: Echo time
TMT: Trail Making Test
TR: Repetition time
VLMT: Verbaler Lern- und Merkfähigkeitstest
